## 8. Statistics

### 8.1 Sample size

Previous similar studies analyzing exercise testing in patients undergoing percutaneous structural heart interventions have included populations of 11 to 30 patients. Based on our current volume of TAVI patients, we estimate we will include one patient per week in each of the study centers, with a final population of 120 patients in the study.

### 8.2 Statistical analysis

Categorical data will be expressed as frequency (%). Quantitative variables will be expressed as mean  $\pm$  standard deviation or median and interquartile range (IQR) depending on their distribution. Categorical variables will be analyzed with Fisher's exact test, in case of repeated measures McNemar test will be applied. Continuous variables will be compared with Student's t-test for independent groups and Mann-Whitney U test according to each variable distribution, in case of repeated measures Friedman test will be applied.

For the primary outcome, we will utilize a multiple linear regression analysis to establish the relationship between baseline characteristics and changes in continuous CPET variables following TAVI. To assess the relationship between these baseline characteristics and CPET values and the qualitative secondary outcomes, we will employ a multiple logistic regression analysis. For the secondary outcome, defined as a composite of death, heart failure readmission, and in-hospital complications, we will use a Cox proportional hazards regression model. A p-value of 0.05 will be considered for statistical significance.

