|                                      | Pacemaker/CRT/ICD                                                                                            |                           | x             |                            |                             |
|                                      | Known atrial fibrillation/flutter                                                                            |                           | x             |                            |                             |
|                                      | COPD                                                                                                         |                           | x             |                            |                             |
|                                      | Diuretic treatment                                                                                           |                           | x             | x                          | x                           |
|                                      | Heart failure treatment: ACE inhibitors, ARBs, sacubitril-valsartan, SGLT-2i, beta blockers, MRA, ivabradine |                           | x             | x                          | x                           |
|                                      | Other heart rate medication: amiodarone, calcium channel blockers, digoxin                                   |                           | x             | x                          | x                           |
| Vitals                               | Heart rate, rhythm, blood pressure, pulse oximetry.                                                          |                           | x             | x                          |                             |
| Echocar-diography                    | Mean aortic gradient, degree of aortic insufficiency, LVEF, RV function, degree of mitral regurgitation      |                           | x             | x                          |                             |
| Bloodwork                            | Prealbumin, albumin, hemoglobin,                                                                             |                           | x             | x                          |                             |

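### The only test named for repeated categorical data, McNemar's, does not fit the graded items (NYHA class, regurgitation degree) unless they are collapsed at a cut that the protocol does not state

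*Protocol*

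**What the plan says.** Protocol section 8.2 assigns tests by variable type. For categorical data it names Fisher's exact test, and then "in case of repeated measures McNemar test will be applied". For continuous data it names the t-test and Mann-Whitney U, and then "in case of repeated measures Friedman test will be applied". Friedman is therefore given to continuous variables, and McNemar stands alone for repeated categorical ones. The threshold is "A p-value of 0.05 will be considered for statistical significance". The linear, logistic and Cox models in the same section relate baseline factors to outcomes; none tests within-patient change in a categorical item.

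Table 1 in section 7 shows which categorical items are repeated:

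- NYHA class: T1, T2 and T3.
- Echocardiography, T1 and T2: "Mean aortic gradient, degree of aortic insufficiency, LVEF, RV function, degree of mitral regurgitation". Two of these five are recorded as a degree.
- Drug items, T1, T2 and T3: "Diuretic treatment", "Heart failure treatment: ACE inhibitors, ARBs, sacubitril-valsartan, SGLT-2i, beta blockers, MRA, ivabradine", and a third row for other heart-rate drugs.

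Section 8.2 states no cut-point, no choice of visit pair, and no multi-category extension such as Bowker or Stuart-Maxwell.

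**The concern.** McNemar's test compares the two discordant cells of one paired 2×2 table. A four-class scale gives a 4×4 table with six pairs of off-diagonal cells, and the 2×2 test uses one pair. An analyst following 8.2 must first turn NYHA class and regurgitation degree into yes/no variables, and the protocol does not say where to split.

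Two things follow. Movement within one side of the cut counts as no change: with a I–II versus III–IV split, a patient going from class II to I, or from IV to III, is treated as unchanged. The result also depends on a cut that the protocol leaves open.

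NYHA change is of some interest here, because section 2 presents NYHA as the usual, subjective way of judging improvement and offers CPET as the objective alternative.

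**Working it through.** The plan gives no figure to reproduce. The sample size, "with a final population of 120 patients in the study", rests on recruitment volume, with no effect size or power. The check is first structural and then an illustration on assumed inputs.

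**Fit of the test (needs two levels and two visits)**

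| Item | Levels | Visits | Fits McNemar as collected? |
|---|---|---|---|
| NYHA class | more than 2 | T1, T2, T3 | No: levels, and visits if all three are compared |
| Aortic insufficiency, mitral regurgitation | more than 2 | T1, T2 | No: levels |
| Drug use, yes/no per class | 2 | T1, T2, T3 | Yes for one visit pair; no as a joint test of three |

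The protocol does not print the number of levels. I take NYHA as I–IV; the argument needs only more than two.

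**Share of improvements lost by collapsing**

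Assume baseline NYHA I/II/III/IV of 5/45/45/5% and an equal chance of a one-class gain from II, III and IV. Only III-to-II crosses a I–II versus III–IV cut:

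lost share = 1 − 0.45 / (0.45 + 0.45 + 0.05) = 1 − 0.474 = 53%.

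**Effect on power**

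Assume 108 pairs (120 × 0.90), a 25% chance of a one-class gain among patients in II–IV, and a 10% chance of a one-class loss among patients in I–III. All these inputs are assumptions. Expected changes:

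- Full scale: improve 0.25 × 0.95 = 23.75% (25.7 patients); worsen 0.10 × 0.95 = 9.5% (10.3 patients).
- Collapsed: downward crossings 0.25 × 0.45 = 11.25% (12.2 patients); upward crossings 0.10 × 0.45 = 4.5% (4.9 patients).

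The improve-to-worsen ratio is the same (2.5 to 1), but fewer than half of the changes remain. Simulated power, with exact two-sided tests at 0.05:

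| Baseline I/II/III/IV | Gain / loss chance | McNemar, collapsed | Sign test, full scale |
|---|---|---|---|
| 5/45/45/5% | 25% / 10% | about 34% | about 69% |
| 30/50/18/2% | 25% / 10% | about 2% | about 26% |
| 5/45/45/5% | 50% / 10% | about 95.5% | about 100% |

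The 25% and 10% apply to patients able to move, not to all patients. In the second row only 0.25 × 0.70 = 17.5% of patients improve, which is why the sign test also falls. There the collapsed scale sees 0.25 × 0.18 = 4.5% crossing down and 0.10 × 0.50 = 5% crossing up, so the improvement disappears altogether.

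Every simulated change is one class. All non-zero differences are then equal in size, so a signed-rank test orders the data as the sign test does.

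**Dependence on the cut**

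In an illustrative paired NYHA table of 120 patients, 75 of whom change class, McNemar retains 36 changes with the cut after class I, 49 after class II and 7 after class III.

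**Yes/no items over three visits**

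If all three visit pairs were tested at 0.05 without adjustment, the familywise error would be 1 − 0.95³ = 14.3% for independent tests. Simulation with correlated visits gives 12.2% to 12.7%. Cochran's Q, a single joint test, gives 4.5% to 4.8%.

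**The case against.** The strongest reply is that nothing the trial sets out to show depends on this test. Section 4 makes change in VO2 max and in VO2 at anaerobic threshold the primary outcome. The secondary outcomes concern predictors and relationships, for which 8.2 names regression models. Change in NYHA class, regurgitation degree or drug use is not among them. This stands, and it limits the severity.

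A second reply is that the cut, the visit pair or a multi-category extension is ordinary SAP detail, and an SAP may exist. This stands in part. A reader might infer that the cut will be chosen after the data are seen; the protocol alone does not show that. But the protocol does not leave the method open. It names one test that cannot be applied to these items as recorded.

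Other stronger readings are tempting and are not supported:

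- *McNemar is wrong for drug use.* For a yes/no drug item at T1 versus T2 it is valid. It fails only as a joint test over three visits.
- *The plan inflates type I error over three visits.* No T1–T3 comparison of these items is promised. The 12–13% describes what would happen if one were made by unadjusted pairs.
- *NYHA is the only symptom measure.* MLHFQ and KCCQ-12 are collected at the same three visits, and section 7 records symptoms separately at six months.
- *The power loss is a property of this trial.* It depends on assumed baseline classes and shifts. With a large shift from the first baseline, both tests exceed 95%.

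**Conclusion.** The point holds, as a minor one. Section 8.2 prescribes McNemar for all repeated categorical data, and NYHA class and the two regurgitation degrees are graded, so the test can be run on them only after collapsing at an unstated cut. The structural part rests on the text of 8.2 and Table 1, plus the assumption that these scales have more than two levels.

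The size is illustrative. With the 5/45/45/5% baseline and a moderate shift, collapsing about halves power (about 34% against 69%). With most patients already in classes I–II it leaves almost none (about 2% against 26%). With a large shift from the first baseline it matters little. No comparable calculation was made for regurgitation degree. The primary outcome and the listed secondary outcomes are unaffected.

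**What to change.** In section 8.2:

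- Limit McNemar to yes/no items compared at two visits.
- Name the Wilcoxon signed-rank test for NYHA class and regurgitation degree at T1 versus T2.
- If all three visits are to be compared, name Friedman or an ordinal repeated-measures model for NYHA class, and Cochran's Q for yes/no drug use.

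Friedman is already in 8.2 for continuous data and needs only to be extended to ordinal items. The cost is about two sentences, with no new data, patients or visits.

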### 4. Objectives and endpoints

#### Primary outcome:

To determine the impact of TAVI on mid-term functional capacity in terms of change in CPET parameters: VO2 max, VO2 at anaerobic threshold.

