### 5. Study design

This is a prospective, multi-center study where we will perform a CPET in patients with severe aortic stenosis before and six weeks after TAVI. There will be no control group, randomization or blinding. This study does not have any intervention other than performing a CPET, frailty assessment and strength tests. In this study we will use a CE (European conformity) marked health product.

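### The only test named for repeated continuous measures is Friedman's, which on two-visit CPET data is the sign test: valid, but blind to the size of each change

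*Protocol*

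**What the plan says.** Protocol section 8.2 assigns tests by type of variable. For unpaired continuous data: "Continuous variables will be compared with Student's t-test for independent groups and Mann-Whitney U test according to each variable distribution". For paired or repeated continuous data the same sentence ends: "in case of repeated measures Friedman test will be applied". That clause sets no condition on the distribution or on the number of visits. For repeated categorical data, "in case of repeated measures McNemar test will be applied".

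Section 5 describes a single-arm study: "There will be no control group, randomization or blinding". The investigators will "perform a CPET in patients with severe aortic stenosis before and six weeks after TAVI". Table 1 in section 7 marks CPET, grip strength, sit-to-stand, echocardiography and bloodwork at T1 and T2 only. The MLHFQ, KCCQ-12, YPAS, Barthel index and NYHA class are also recorded at T3.

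The primary outcome in section 4 is "To determine the impact of TAVI on mid-term functional capacity in terms of change in CPET parameters", namely VO2 max and VO2 at anaerobic threshold. The model that section 8.2 attaches to it is a "multiple linear regression analysis to establish the relationship between baseline characteristics and changes in continuous CPET variables following TAVI".

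**The concern.** Without a control group, the before-after contrast within patients is the only comparison that can show whether functional capacity changed. The one test that section 8.2 offers for such a contrast on a continuous variable is Friedman's, which is designed for three or more related measurements. On two it uses only the direction of each patient's change: a gain of 0.1 and a gain of 5 ml/kg/min count the same, although the protocol itself defines response by size, at 2.5 ml/kg/min.

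Two things are at stake. One is power: N = 120 rests on recruitment volume, with no power calculation that could absorb a loss. The other is estimation: the sign test does not lead to a mean change with a confidence interval, which is the result a reader of this study will look for.

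**Working it through.** **Inputs.** From the protocol: n = 120 (section 8.1); significance level 0.05 (section 8.2; two-sided is assumed, as sidedness is not stated); k = 2 visits for CPET (section 5, Table 1). The protocol gives no effect size, SD of the change, power or dropout, so there is no planned power to reproduce. Assumed: a standardized mean change d (mean change divided by SD of the changes) of 0.2 to 0.4, and 96 to 120 evaluable pairs.

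**Step 1: Friedman with two visits is the sign test.** Each patient's two values are ranked 1 and 2. If S of n patients rise and there are no ties, the rank sums are n + S and 2n − S, and

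Q = 12/(n·2·3) × [(n + S)² + (2n − S)²] − 3n·3 = (2S − n)²/n,

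which is the squared z of the sign test. Check with n = 120, S = 75: (150 − 120)²/120 = 900/120 = 7.5, and the rank formula also gives 7.5.

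**Step 2: validity.** The test rejects when Q > 3.841. At n = 120, S = 70 gives 20²/120 = 3.33 and S = 71 gives 22²/120 = 4.03, so it rejects when 71 or more patients change in the same direction. The exact two-sided binomial probability of this with no effect is 5.5%. Simulated type I error over n = 96 to 120 was 4.3% to 5.4%. Validity is not in question.

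**Step 3: efficiency with normal differences.** Sign test against paired t-test: 2/π = 0.637, so 120 pairs do the work of 120 × 0.637 ≈ 76. Sign test against Wilcoxon signed-rank: 2/3, so 120 × 2/3 = 80.

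**Step 4: power with normal differences.** A patient rises with probability p = Φ(d). At d = 0.258, p = 0.602; the exact binomial power of the rule in Step 2 is 62.8%, against 80.0% for the paired t-test. At d = 0.298, p = 0.617, and the figures are 74.9% and 89.9%. Simulation (20,000 replicates) adds Wilcoxon:

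| Pairs | d | Paired t | Wilcoxon signed-rank | Friedman/sign |
|---|---|---|---|---|
| 120 | 0.2 | 58% | 56% | 43% |
| 120 | 0.256 | 80% | 78% | 62% |
| 120 | 0.3 | 90% | 89% | 75% |
| 120 | 0.4 | 99% | 99% | 94% |
| 96 | 0.2 | 50% | 48% | 35% |
| 96 | 0.3 | 83% | 81% | 66% |

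In sample-size terms, at d = 0.256 the sign test needs n = [(1.96 × 0.5 + 0.84 × √(p(1 − p)))/(p − 0.5)]² with p = 0.601, about 190 pairs, to reach the 80% power that the paired t-test has with 120.

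**Step 5: other shapes.** Efficiency of the sign test against the t-test is 0.82 for logistic differences, 0.96 for t with 5 degrees of freedom, 1.62 for t with 3, and 2.0 for Laplace. Simulated power at n = 120, d = 0.256, Wilcoxon against Friedman/sign: 87% v 79% (t5), 96% v 94% (t3), 91% v 93% (Laplace). The loss against the t-test can therefore disappear or reverse, while Wilcoxon stays ahead of the sign test in all but the Laplace case.

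**The case against.** The strongest reply is that the primary outcome has its own analysis. The multiple linear regression uses the size of each patient's change and gives estimates with intervals, while the Friedman clause sits in a general paragraph and is tied to no endpoint. This stands in part. A reader might infer that Friedman is the declared primary analysis; the protocol does not say so. But the regression is described as relating change to baseline characteristics. With suitably centred covariates its intercept would estimate the mean change, yet section 8.2 mentions neither that nor any other test or interval for it.

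Other limits also stand:

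- A reader might infer that no effect size will be reported. Section 8.2 plans mean ± SD or median and IQR, so what is missing is an inferential estimate of the change.
- A flat statement that a third of the information is lost would go too far. It assumes near-normal differences, and the protocol gives no distribution or SD for the change. The gap is also small if the effect is large (99% v 94% at 0.4 SD).
- Friedman may have been meant only for non-normal variables. The text does not say this, and even so the two-visit non-normal case would usually go to Wilcoxon signed-rank, while the normal case would have no paired test.
- For the questionnaires recorded at three visits Friedman is a legitimate choice. A mixed model is an option there, not a correction.
- A reader might infer that four-level NYHA class will be put through McNemar's test. Section 8.2 gives McNemar for repeated categorical data in general, but no such NYHA analysis is specified and NYHA is not a listed outcome.

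**Conclusion.** The point holds for continuous variables measured at two visits. Section 8.2 fixes a test that there reduces to the sign test, and it names no paired alternative. Under roughly normal differences and a two-sided 0.05 level, efficiency is about 0.64 against the paired t-test and 0.67 against Wilcoxon signed-rank; with all 120 pairs evaluable, power is about 63% where the paired t-test has 80%, and about 75% where it has 90%. The d values behind these two figures are reference points, not trial inputs.

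It matters because, as written, no other stated analysis addresses whether VO2 max and VO2 at anaerobic threshold change after TAVI. It would be wrong to read this as a flaw that biases the result or inflates false positives: the type I error is close to nominal. It should be fixed before analysis, but it does not make the planned analysis invalid.

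**What to change.** In section 8.2, replace the repeated-measures clause for continuous variables with wording to this effect:

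- **Measured at T1 and T2 only**, including change in VO2 max and VO2 at anaerobic threshold: paired t-test with mean change and 95% confidence interval; Wilcoxon signed-rank test if the differences are clearly non-normal.
- **Measured at T1, T2 and T3:** Friedman's test may stay; a mixed model is optional.
- **Categorical:** keep McNemar for binary pairs. If change in NYHA class is to be tested, name a paired ordinal method such as Wilcoxon signed-rank.

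State also that the paired analysis addresses whether CPET values change, and that the multiple linear regression addresses which baseline factors go with the change. The cost is a few sentences; no patients, visits or measurements are added.

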Surgical risk scores such as the European System for Cardiac Operative Risk Evaluation II (EuroSCORE II) and the Society of Thoracic Surgeons (STS) predicted risk of mortality (PROM) score have been validated for surgical interventions. However, they do not contemplate frailty and other comorbidities that impact outcomes in transcatheter procedures. Hence, new scores have been specifically developed to estimate the risk in patients undergoing TAVI (PARTNER, FRANCE 2), although there is no standardized method to evaluate the potential benefit of the procedure. Furthermore, clinical improvement is mostly assessed by the patient's self-reported

change in symptoms, and the clinician's assignment of a New York Heart Association (NYHA) class based on this information. However, it is well established that interobserver agreement of NYHA classification is only around 55%, and there is no consistent method to assign a NYHA class. Therefore, clinical improvement is still essentially a subjective measurement.

In this scenario, CPET, a well-established tool in the preoperative risk assessment of surgical patients, could be a promising tool not only to objectively determine the degree of improvement in functional capacity after TAVI but also to predict the clinical response to TAVI. CPET has been shown to be useful in determining exercise-limiting factors and pathophysiologic mechanisms, and assessing the contribution of cardiovascular, pulmonary and muscular etiology in coexisting disease.

We believe the utility of performing CPET, along with strength tests and frailty scores, in these patients is potentially two-fold. Firstly, identifying which patients have an objective improvement in functional capacity, and have therefore truly benefited from TAVI. Secondly, predicting which group of patients will show this improvement. This could open a door to implementing these strategies in a systematic way to aid in future decisions to proceed with TAVI or not. Identifying patients who are unlikely to benefit from TAVI in their current state could prompt us to offer alternatives that target their specific limitations and needs.

The present study aims to: 1) characterize the mid-term exercise tolerance response to TAVI, and 2) determine the clinical and functional factors that determine the magnitude of this response.

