#### Secondary outcomes:

- To identify clinical and functional pre-TAVI factors that predict improvement in functional capacity after TAVI (i.e., VO2 max increase > 2.5 ml/kg/min).
- To identify clinical, echocardiographic and functional pre-TAVI variables that predict improvement in quality of life.
- Relationship between pre-TAVI CPET parameters and in-hospital complications.
- Relationship between pre-TAVI CPET parameters and complications at 6 weeks.
- Relationship between echocardiographic and CPET parameters after TAVI.
- Relationship between frailty and post-TAVI clinical outcomes.

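### The analysis named for the primary outcome asks which baseline factors go with CPET change, not whether or by how much VO2 changed after TAVI

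*Protocol*

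**What the plan says.** The end of section 2 gives two separate aims: "1) characterize the mid-term exercise tolerance response to TAVI, and 2) determine the clinical and functional factors that determine the magnitude of this response". Section 3 keeps the split: Hypothesis 1 is that the benefit can be measured by CPET, and Hypothesis 2 is that pre-TAVI factors predict the degree of response.

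Section 4 gives the primary outcome as "To determine the impact of TAVI on mid-term functional capacity in terms of change in CPET parameters", naming VO2 max and VO2 at anaerobic threshold. Prediction appears among the secondary outcomes: "To identify clinical and functional pre-TAVI factors that predict improvement in functional capacity after TAVI", with improvement defined there by a VO2 max gain above 2.5 mL/kg/min.

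Section 5 describes one group: "There will be no control group, randomization or blinding". The investigators will "perform a CPET in patients with severe aortic stenosis before and six weeks after TAVI", and Table 1 schedules CPET at T1 and T2 only.

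Section 8.2 has two relevant parts. The general paragraph provides means with SDs or medians with IQRs, and says of continuous variables that "in case of repeated measures Friedman test will be applied". The next paragraph assigns methods to outcomes: "For the primary outcome, we will utilize a multiple linear regression analysis to establish the relationship between baseline characteristics and changes in continuous CPET variables". Logistic regression goes to the qualitative secondary outcomes. The significance level is given as "A p-value of 0.05 will be considered for statistical significance".

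**The concern.** The primary question is about an average: did VO2 change between T1 and T2, and by how much? The method assigned to it is about variation around that average: which patients changed more than others. These are different quantities, and the protocol itself separates them in its aims, hypotheses and outcome list. With no control group, the within-patient change is the only contrast that can answer the primary question, yet the analysis labelled primary does not ask for it.

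A team following section 8.2 could present predictor coefficients as the primary result. The size of the change would then be left to descriptive summaries and a general-purpose rank test. This goes beyond detail that a protocol may leave to an SAP, because the protocol does name a method for its primary outcome and that method addresses another aim.

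**Working it through.** **1. No planned figure to reproduce.** Section 8.1 bases the 120 patients on recruitment volume and gives no effect size, SD, power or dropout. The check is therefore structural first, then one of precision.

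**2. What the regression can show.** Let d be a patient's change (T2 minus T1) and fit d = b0 + b1·x1 + … + bp·xp + error. Adding a constant c to every d is matched exactly by replacing b0 with b0 + c. Residuals, slopes, slope p-values, the overall F-test and R² do not move.

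A simulated data set confirms this (n = 120, five baseline covariates, residual SD 3):

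| Constant added (mL/kg/min) | Overall F-test p | R² | Sample mean change | Paired t-test p | Intercept, covariates centred | Intercept, covariates uncentred (mean about 70, SD about 10) |
|---|---|---|---|---|---|---|
| 0 | 0.086 | 0.080 | -0.51 | 0.11 | -0.51 | -5.94 |
| 1 | 0.086 | 0.080 | 0.49 | 0.13 | 0.49 | -4.94 |
| 2.5 | 0.086 | 0.080 | 1.99 | 1 × 10⁻⁸ | 1.99 | -3.44 |

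The predictor results are identical in all three rows, while the average change runs from about -0.5 to about 2.0. Only the intercept moves. It equals the mean change when covariates are centred, but section 8.2 mentions neither centring nor an inference on the intercept.

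**3. What the general Friedman sentence can show.** With n pairs, two time points, no ties and k patients improving, the Friedman statistic is (2k - n)²/n on 1 degree of freedom, which is the two-sided sign test. It uses the direction of each change and discards its size, so it yields no estimate or interval in mL/kg/min. Under normality its asymptotic efficiency relative to the paired t-test is 2/π = 0.64, so 120 pairs carry roughly the information of 0.64 × 120 ≈ 77 in a t-test.

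Simulated power (20,000 runs, N = 120, assumed SD of change 3, two-sided 0.05):

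| Mean change (mL/kg/min) | Sign/Friedman | Paired t |
|---|---|---|
| 0.50 | 0.33 | 0.45 |
| 0.75 | 0.61 | 0.78 |
| 1.00 | 0.84 | 0.95 |

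**4. What a paired estimate would deliver.** The SD of change is not in the protocol, so a range is assumed. Half-width = t(0.975, N-1) × SD/√N. Detectable mean change at 80% power = (1.96 + 0.84) × SD/√N. For example, with N = 120 and SD 3: 1.98 × 3/10.95 = 0.54, and 2.80 × 3/10.95 = 0.77.

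| Assumed SD | Half-width, 120 pairs | Detectable, 120 pairs | Half-width, 96 pairs (20% loss assumed) |
|---|---|---|---|
| 2 | 0.36 | 0.51 | 0.41 |
| 3 | 0.54 | 0.77 | 0.61 |
| 4 | 0.72 | 1.02 | 0.81 |
| 5 | 0.90 | 1.28 | 1.01 |

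All values are in mL/kg/min. Two-sided testing is assumed, because section 8.2 does not state sidedness.

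**The case against.** The best defence is that section 8.2 should be read whole. VO2 is a continuous measure taken twice, so the general paragraph already gives summaries at each visit and a within-patient test. A reader might infer from the regression sentence that Hypothesis 1 has no test at all, or that the report could not say whether capacity changed. The document does not support that: the Friedman sentence can supply a p-value, and the visit summaries give a rough indication of size. What remains is narrower. That test is not attached to the primary outcome, the next paragraph attaches something else, and neither the test nor the summaries give the within-patient change with its uncertainty.

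A second defence is that the regression intercept could carry the mean change. It could with centred covariates, so calling it meaningless would go too far. However, the stated purpose of the model is the relationship with baseline characteristics, and nothing points to the intercept.

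A reader might also call the linear regression simply the first secondary objective under the wrong label. That is inexact: the objective is defined by a responder cut-off, whereas a model of continuous change fits the second aim in section 2.

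Finally, a reader might see a contradiction between mid-term in the objective and the six-week CPET. The protocol fixes the test at six weeks throughout and gives no other meaning to the term, so this is only wording.

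**Conclusion.** The concern holds in this limited form: section 8.2 ties to the primary outcome a method that answers the predictor question, and the only pre/post test is a general one that estimates nothing. The mismatch rests on the protocol's own text and on exact algebra, not on any assumed figure.

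The power loss from the Friedman route (for example 0.61 against 0.78) assumes roughly normal changes, an SD of 3 and a mean change of 0.75. The half-widths of 0.36 to 0.90 mL/kg/min assume an SD of change of 2 to 5 and 120 complete pairs. They show what the planned data could provide; they do not measure harm already done. The point should be settled before analysis, because it decides which number the study presents as its main result.

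**What to change.** In section 8.2, state the primary analysis as the mean within-patient change from T1 to T2 with a 95% CI and a paired t-test, for both VO2 max and VO2 at anaerobic threshold. Name the Wilcoxon signed-rank test as the alternative if changes are clearly non-normal. Neither parameter should be dropped, since section 4 names both.

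Relabel the multiple linear regression as a secondary analysis of what determines the magnitude of the change (aim 2 in section 2). Keep logistic regression for the responder objective, which is defined by a VO2 max gain above 2.5 mL/kg/min.

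The cost is a rewritten paragraph in section 8.2. The visits, tests and sample size stay as they are, and no new data are needed.
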